### Secondary exploratory aim: testing predictors

We hypothesized that the susceptibility to both body illusions, that is body image flexibility, will predict other key psychological constructs that have shown relations with ED, such as interoceptive body awareness (i.e., the ability to identify, access, understand, and respond appropriately to the patterns of internal signals) [14, 15] and sensory-processing sensitivity (i.e., the tendency to process stimuli and information more strongly and deeper than others [33]). Likewise, given the novelty of the topic, the following hypothesis are descriptive–exploratory in nature:

**Hypotheses 5 (H5)**: There is a relationship between body position/size measures and interoceptive body awareness as well as sensory-processing sensitivity.

**Hypotheses 6 (H6)**: Body position/size measures may have an effect on interoceptive body awareness and sensory-processing sensitivity.

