For example, Mussap and Salton [14] noted, one explanation for individual differences in response to cognitive-behavior therapies may reflect differences in pre-existing levels of body-image flexibility (i.e., ability to openly perceive thoughts or sensations concerning the body without acting on or changing them) [14]. This line of reasoning is in accordance with a recent meta-analysis (N = 62) which indicated that higher body-image flexibility is associated with lower levels of body-image problems and ED symptomatology [31]. Thus, body-image flexibility may arise as a key psychological construct that may be enhanced during psychological interventions [31]. As such, both body illusions (affecting finger and waist mental representations) could be useful to potentially identify participants who will be most responsive to behavioural therapies, as those with heightened body-image flexibility. Given the lack of research, there is a need to test the association between body-image flexibility and key psychological constructs related to ED symptomatology in this area [31].

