**Hypotheses 4 (H4)**: Participants with subthreshold ED symptomatology, as compared to people without ED symptomatology, will experience the finger illusion but not the waist illusion, suggesting that the experience of the illusion is linked to the emotional salience of the body part rather than the nature of the auditory signals.

H4 hypothesizes that participants with subthreshold EDs symptomatology will experience the illusion for the finger (not emotionally salient body part), replicating previous research (see [25]) but not for the waist (emotionally salient body part). In that case, the experience of the illusion will not be linked to the nature of the auditory signals (natural sound vs. artificial sound), but to the emotional salience of the body part (finger vs. waist).

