### General experimental procedure

Table 1 shows an overview of study measures and data collection time points and Fig. 3 shows a schematic representation of the experimental procedure. After reading the information sheet and signing the information consent, participants will complete the S-EDE-Q. Participants eligible to take part will be invited to the lab at Loyola Andalucia University. The experimental procedures will be implemented, and all data will be collected, by a postgraduate Ph.D. researcher trained by senior members of the research team. After reading the information sheet and signing the information consent, demographic data (age and BMI) will be collected. Later, participants will complete two questionnaires related to the secondary aim (see Table 2). The Multidimensional Assessment of Interoceptive Awareness Scale (MAIA) (to assess interoceptive body awareness) and the Highly Sensitive Person Scale (HSPS) (to assess sensory-processing sensitivity). The same participants will complete both Experiments 1 and 2.

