### Sample size considerations

As these analyses are intended to generate future confirmatory hypotheses, no sample size calculation was conducted. As Jones et al. [53] noted, sample size calculation may be of little value in early exploratory studies where there is a lack of previous research. In an exploratory study, the primary focus is on generating new research questions, identifying patterns and trends, and identifying potential areas for further research, rather than on testing a specific confirmatory hypothesis. As such, the sample size in an exploratory study may not be determined based on statistical power or precision and could be relatively small. Instead, the sample size may be based on the need to obtain a sufficient amount of data to allow for the exploration and identification of meaningful patterns and trends.

In this regard, a total of 100 participants (50 participants in each group) will allow us to gain an exploratory understanding between body perception and non-naturalistic auditory information in participants with subthreshold ED symptomatology. This sample size is the minimum recommended by Brysbaert [54] to seek differences between groups and is also between 30 and 150 participants, that is the sample size usually recommended in exploratory study designs with non-probability sampling [55]. To this end, and based on norms for the Spanish version of the Eating Disorders Examination Questionnaire (S-EDE-Q), we will screen approximately at least 450 young adult females [39].

Due to the limited sample size, we acknowledge that the statistical power for each of the hypotheses proposed in this study to detect differences between groups might not be sufficient according to the traditional standards in experimental psychology (effect size = 0.4, power = 0.80 and alpha value = 0.05) [54]. Therefore, the results should be taken with caution and should be contextualized within an exploratory framework. In case of meaningful results, the present exploratory study will provide the necessary foundation for a formal sample size calculation for a future confirmatory larger-scale study.

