#### Secondary aim: testing predictors

Only outcomes showing significant bivariate correlations with the predictor will be included in the final multivariate logistic regression model and these selected variables will be forced into the model using enter method. For these bivariate correlations, we will use Spearman’s Rho for non-parametric data and Pearson’s r product-moment correlation coefficient for parametric data. Prior to the analysis we will check for multicollinearity, homoscedasticity, normality of the residuals as well as independence/variance of the residuals and any bias influencing the model. If these assumptions do not hold, then non-linear regression analysis will be used.

For each experiment, we will conduct multiple linear regression analysis on the entire sample to explore the predictive role of body-image flexibility (estimation of body position/size measures as inputs) on different outcomes such as interoceptive body awareness (MAIA) and sensory-processing sensitivity (HHSPS).

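### The secondary aim reads susceptibility to the finger and waist illusions as one trait, but the planned per-experiment regressions never test whether the two agree, so conflicting results would have no defined meaning

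*Protocol article*

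**What the plan says.** The secondary aim (Aim and hypothesis, Secondary exploratory aim) hypothesises that "the susceptibility to both body illusions, that is body image flexibility" will predict interoceptive awareness and sensory-processing sensitivity. The Background takes the same view and says that "both body illusions (affecting finger and waist mental representations) could be useful to potentially identify participants" likely to respond to behavioural therapy, meaning those with high flexibility.

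H4, under the primary exploratory aim, proposes that the subthreshold participants "will experience the finger illusion but not the waist illusion". That group is half of "a total of 100 participants (50 participants in each group").

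The analysis section (Statistical analyses, Secondary aim: testing predictors) says: "For each experiment, we will conduct multiple linear regression analysis on the entire sample". The predictors are described as "body-image flexibility (estimation of body position/size measures as inputs"). The General experimental procedure adds: "The same participants will complete both Experiments 1 and 2".

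The other planned analyses do not connect the tasks. The 2 × 3 ANOVAs have group and feedback condition as factors, but not body part. The complementary correlation is with EDE-Q. The screening correlations for the regressions are between outcome and predictor.

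**The concern.** The construct in the aim and the model in the analysis section do not match, in two ways.

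First, a claim about one person-level trait measured by two tasks assumes that people who respond strongly on one task tend to respond strongly on the other. The plan assumes this and does not examine it, while one of its own hypotheses describes a situation in which it may fail. If the finger regression is positive and the waist regression is null, either could be reported as the answer on body-image flexibility.

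Second, susceptibility is a change in perceived size between tones. As written, the inputs are the estimates themselves. An estimated finger length or waist width depends on actual size and on general over- or underestimation as well as on the tone. A coefficient for such an estimate does not show that susceptibility to an illusion predicts anything.

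The stake is what the secondary aim can conclude, and what a later confirmatory study would carry forward: one trait or two task-specific responses.

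**Working it through.** The plan gives no figure on this point to reproduce. The check sets the text side by side and then sizes the consequence under stated assumptions.

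**Text**
- Construct: one, covering both illusions (secondary aim, Background).
- Models: one set per experiment, groups pooled, no composite score, no group term stated.
- Link between tasks: none in the ANOVAs, the EDE-Q correlation or the screening correlations.
- Data for a link: available, since every participant completes both experiments.

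**Direction of the scores**
H3 names the illusions as finger elongation and a shrinking waist. With ascending minus constant on both tasks, a strong illusion gives a positive finger score and a negative waist score. A single trait would then produce a negative correlation and regression coefficients of opposite sign. The scores have to be oriented first: ascending minus constant for the finger, constant minus ascending for the waist. The Background also links ascending pitch with growing size, so the waist direction needs to be fixed in writing.

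**How often would the two regressions disagree on significance?**
From the documents: n = 100, 50 per group. Assumed: two-sided 5% test of a correlation, true finger-outcome correlation 0.30.
- Power by Fisher z, SE = 1/√97 = 0.1015. For r = 0.30, z = 0.3095 and power = Φ(0.3095/0.1015 − 1.96) = Φ(1.09) = 0.86. For r = 0.15, z = 0.1511 and power = Φ(1.49 − 1.96) = 0.32.
- One trait behind both tasks, both correlations 0.30: if the tests were independent, disagreement = 2 × 0.86 × 0.14 = 0.24.
- Waist scores carrying no trait information in the subthreshold half, no group mean differences: pooled waist-outcome correlation = (0.30 + 0)/2 = 0.15. If independent, disagreement = 0.86 × 0.68 + 0.14 × 0.32 = 0.63.

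The tests are not independent, so a simulation was run (20,000 runs per scenario, assumed finger-waist correlation 0.3 to 0.7 under one trait, halved by the dissociation):

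| Assumed r with outcome | One trait | No waist information in subthreshold half |
|---|---|---|
| 0.2 | 26-41% | 45-48% |
| 0.3 | 14-21% | 58-62% |
| 0.4 | about 2% | 47-48% |

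**Why group belongs in the model**
Add assumed group differences of 0.8 SD in the waist effect and 0.5 SD in the outcome. At r = 0.3 the pooled waist-outcome correlation becomes about 0.04 or 0.23, depending on the direction of the outcome difference. Over all settings disagreement runs from 22% to 84%. Point estimates differ in sign in up to 49% of runs. Both results significant with opposite signs occurs in 1% of runs or fewer.

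**What the missing correlation could show**
For an assumed finger-waist r of 0.30:
- n = 100: 0.3095 ± 1.96 × 0.1015, back-transformed, gives a 95% CI of 0.11 to 0.47; power 86%.
- n = 50 (one group): SE = 1/√47 = 0.1459, 95% CI 0.02 to 0.53; power about 56%.
- n = 100 with r = 0.15: power about 32%.

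**The case against.** The strongest reply is that the plan contains no contradiction. H4 is about whether a group shows an average waist effect, and the secondary aim is about differences between individuals. A group mean near zero leaves the between-person variance, and its correlation with the finger effect, open. This stands. A reader might infer from H4 that the same woman must be flexible by one task and inflexible by the other. The documents do not support that, because it draws individual results from a group mean.

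Nor do they make discordance the expected result. All hypotheses are labelled exploratory and they compete: H2 predicts stronger illusions in the subthreshold group, H3 unusual patterns, H4 a separation by body part.

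It can also be said that H5 and H6 refer to position/size measures rather than a trait score, and that separate regressions would expose a dissociation instead of hiding it. That is partly right, and nothing in the text plans selective reporting. But the analysis section itself puts the trait label on the inputs of each regression, so the label is part of the stated analysis.

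Finally, an article may leave a correlation or a rule for discordant results to a fuller plan. Absence alone would not be a point. The point is that the model structure is stated, and it does not fit the stated construct. The entry of position/size estimates may be shorthand for change scores; if so, one sentence settles that part.

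**Conclusion.** The concern holds in a limited form and should be addressed. The plan defines one trait across two tasks, models the tasks separately under that one name, and does not examine whether they agree. A result in which one task predicts and the other does not would have no defined meaning for the trait. Depending on assumptions the documents do not supply, that pattern appears in about 2% to 41% of studies if one trait exists, and in about 45% to 62% if the waist score is uninformative in the subthreshold half without mean differences.

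Three stronger readings should be avoided:
- That the trait will get opposite answers. Two significant results of opposite sign are rare (1% of runs or fewer); conflicting is the right word.
- That two experiments by two outcomes give four tests and an 18.5% chance of a false positive (1 − 0.95^4). That measures multiplicity rather than the mismatch of construct and model, and four is not the plan's count: Data management defines nine finger and three waist summary scores, and outcomes are screened before modelling.
- That the missing correlation would be decisive. It is reasonably informative in the pooled sample at r = 0.30, but imprecise within groups and weak if the true value is near 0.15.

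The aim is secondary and exploratory, so the effect is on interpretation and not on a confirmatory conclusion.

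**What to change.** 1. For each task, define one tone-change score, oriented so that a higher value means a stronger illusion in that task's hypothesised direction (finger elongation, waist shrinking). State the contrast and the direction in advance.
2. Report the finger-waist correlation of these scores with its 95% CI, overall and descriptively by group, noting that estimates at n = 50 will be imprecise.
3. Use these scores, with group, as predictors of MAIA and HSPS in place of the position/size estimates.
4. Report both tasks together, as finger-illusion susceptibility and waist-illusion susceptibility. Reserve body image flexibility for the case where the oriented scores are positively associated.
5. Optional: one model per outcome with both scores and a 2-df joint test. If both scores reflect one trait, each mutually adjusted coefficient loses the shared part, so the joint test should be read before the single coefficients.

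The cost is a change of wording, a small amount of extra exploratory analysis and possibly a narrower trait claim. No new data are needed.

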## Material and methods

The ethics committees of the University of Loyola and of Junta de Andalucía have approved the present study, which will be performed in accordance with the ethical standards in the 1964 Declaration of Helsinki and its later amendments. All participants will provide informed consent to take part in the study.

## Participants

The experiment will be conducted individually in a quiet laboratory room [see Additional file 1, section A]. In keeping with previous literature and to facilitate the comparison and interpretation of the results because of the variability shown in related measures, the sample will comprise young adult females (sex assigned at birth) in the 18–24 age range, where the prevalence of EDs in this population is the highest [34]. However, it should be pointed out that previous evidence has reported high prevalence of EDs not only in female samples but also in other populations such as in men or gender diverse individuals [35–37]. Additionally, we decided to focus on the waist because this body part has been shown to be particularly emotionally salient for females and a reliable indicator of body mass index (BMI) [4, 38]. Participants will be recruited through public advertisements and social media posts (convenience sampling) and they will be paid or compensated with grade points for their time. To split the sample into participants with and without ED symptomatology, the Spanish Eating Disorder Examination Questionnaire (S-EDE-Q) [39]) will be administered (see Table 1 for more details). The pre-screening will allow to form two groups of similar size: once the desired participant sample size has been reached for one of the groups, only participants falling into the other group defined for the study will be invited to take part. The S-EDE-Q have demonstrated good psychometric properties in young female adults in Spain [39]. A global EDE-Q score ≥ 2.8 has been shown to provide an optimal trade-off between sensitivity and specificity when it is used for screening in primary care [40]. Available resources for participants will include psychoeducation and support for body image and eating-related concerns, provided by a team member. The availability of these resources will be specified in the informed consent. Moreover, to not assume that all individuals are cis-gender, gender identity will be assessed through an additional question.

**Table 1 Tab1:** Overview of study measures and data collection timepoints

Measure	Description	Baseline	Experiment	
			1	2
Demographic data	Participants’ age. In addition, BMI will be calculated with the following formula: BMI = weight (kg)/(height (m)^2^) following the World Health Organization’s criterion [45]	X		
Information consent	Written informed consent	X		
S-EDE-Q†	To assess body EDs psychopathology. Self-administered questionnaire composed of 28 items using 7-point Likert scales ranging from 0 (not at all) to 6 points (markedly) about the previous 28 days. Four subscales are measured, including: dietary restraint (5 items), shape concerns (8 items), weight concerns (5 items), and eating concerns (5 items). For each subscale, the score ranges from 0 and 6 points. Participants will be grouped according to a global index score which is the average of the four subscale scores. As in Mond et al. [36], we will use a cut-off point ≥ 2.8 as clinically significant. Higher scores indicating a higher ED pathology. The S-EDE-Q have shown adequate internal consistency (Cronbach’s alpha ≥ .81 for all subscales), acceptable sensitivity (≥ 0.95), specificity (≥ 0.90), and positive (≥ 0.59) and negative (≥ 0.99) predictive values, and positive and significant correlation (≥ 0.70) with EDE diagnoses	X		
HSPS‡	To assess the tendency to process stimuli and information more strongly and deeply than others (sensory-processing sensitivity). Self-administered questionnaire composed of 27 items using 7-point Likert scales ranging from 0 (not at all) to 6 points (markedly). Five subscales are measured including: (1) sensitivity to overstimulation (9 items); (2) aesthetic sensitivity (6 items); (3) low sensory threshold (5 items); (4) fine psychological discrimination (4 items); (5) harm avoidance (3 items). For each subscale, the score ranges from 27 to 189 points. Higher scores indicate higher sensitivity level. A total global score will be obtained by averaging the five subscales. The HSPS have shown adequate internal consistency (Cronbach’s alpha ≥ 0.81 for all subscales) and construct validity in the adult Spanish population	X		
MAIA§	To measure interoceptive body awareness. Self-administered questionnaire composed of 32 items using 6-point Likert scales ranging from 0 (never) to 5 points (always). Eight subscales are measured, including: (1) noticing (3 items); (2) not-distracting (2 items); (3) not-worrying (2 items); (4) attention regulation (7 items); (5) emotional awareness (5 items); (6) self-regulation (4 items); (7) body listening (3 items) (8) trusting (3 items). It generates a total direct score that ranges from 0 to 160 points. Higher scores indicate higher interoceptive awareness. A total global score will be obtained by averaging the six subscales. The MAIA have shown adequate internal consistency (Cronbach’s alpha 0.64 to 0.83 for all subscales)	X		
Auditory trials	Presented in four conditions: an anchor task (20 trials); a practice task (3 trials); an experimental block (30 trials) and a questionnaire block (3 trials)		X	X
Estimation of body position (finger/waist)	To assess estimation of location or position of fingertip/knuckle (allowing to calculate the estimated finger length can be calculated) and waist width after each auditory experimental trial		X	
Confidence task	It has been found that the reliability of perception might be linked to subjective rather than objective accuracy [41]. For example, previous studies using body illusions report that confidence was not accompanied by increases in objective accuracy (i.e., [42, 43]). Therefore, to assess the reliability of their estimations, after each auditory experimental trial, the feeling of confidence with the estimation of body part position will be explicitly assessed by asking the participants: “From one to seven, how confident are you of your estimation?” (7-point Likert scale)		X	X
Body feelings questionnaire (finger/waist) [25]	To assess subjective feelings about their finger/waist after the trials (susceptibility to the illusion). Participants will respond to a questionnaire containing 7-point Likert-type response items ranging from 1 (strongly disagree) to 7 (strongly agree) (Finger: 14 items; Waist: 13 items). In addition, a range of figures representing finger/waist will be presented. Each figure shows a whole hand/trunk selectively shrunk or elongated. Participants will be asked to choose one of the figures to describe the subjective feeling of the size of their finger/waist when listening to the sound. [see Additional file 2 and 3 for more details]		X	X
Body visualizer task [44]	To assess the ability to accurately estimate body size (body size discrepancy) as well as the effects of sound feedback on perceived body size. Participants will adjust the weight related dimension of the body of a 3D avatar displayed on the screen to correspond to their perceived body size. Accuracy will be calculated according to the formula (estimated/actual body size) × 100 also-called body perception index (BPI) [45]. Specifically, a negative value represents an underestimation, whereas a positive value represents an overestimation	X		X

Body weight will be measured to the nearest 0.1 kg/% by means of a calibrated digital body fat scale (Sinocare CW 286). The Body feelings questionnaire will be directly built into Google Form and completed on a 10.1″ Android tablet (Lenovo M10)

^†^Spanish Version of the Eating Disorder Examination Questionnaire [46]

^‡^Spanish version of the Highly Sensitive Person Scale [47]

^§^The Multidimensional Assessment of Interoceptive Awareness [48]

Inclusion criteria will be: (a) normal (or corrected) auditory acuity; (b) sex: females (sex assigned at birth); (c) females within the healthy range of BMI (between 18.5 and 24.9) in order to reduce the likelihood of medical comorbidities that could affect the results (according to the World Health Organization index (WHO) [49]). Nevertheless, we recognize that weight/body mass index is not the sole predictor of potential co-occurring medical conditions. By doing so, we also avoid a potential confounding variable reported by [24]. This is in line with the criteria of healthy participants usually used in the field of eating disorders and body illusions research (e.g., [16]). Exclusion criteria: (a) lifetime history or presence of any significant brain injury, neurological condition, auditory pathology; (b) lifetime history or presence of a mental illness measured by self-report measures and screening questions; (c) lifetime history of underweight or overweight; (d) current use of psychotropic drugs (e.g. antidepressants) or intake of recreational synthetic or natural drugs; (e) inability to understand Spanish; (f) inability to provide consent; (g) out of age range; (h) pregnant status.

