#### Experiment 1 procedure: Finger

First, the length of the index finger of the participant’s right hand will be measured by the experimenter using a vernier calliper from the proximal crease at the base of the finger to the tip of the finger. Next, participants will be required to complete an "anchor" task. In this task, participants will be asked to press and pull out their right index fingertip with their left hand twenty times, an action that will trigger the ‘anchoring’ tone on each occasion. After completing the anchor task, participants will complete a practice task, one trial for each feedback condition.

In each practice trial, participants are required to stare straight at the red fixation point and complete the simple action of pressing and pulling their right index fingertip with their left hand while keeping the right index finger in a fixed position (straight against the plastic panel and metal bar, see Fig. 1). One of the three experimental tones ('ascending,' 'descending,' or 'constant') is triggered by the pressing/pulling action. Participants are instructed to continue pressing and pulling their fingers until the sound is no longer audible and, once the sound stops, to relax their left hand while continuing to grasp their right finger with the left hand. They will be then asked to estimate the position of their right fingertip and knuckle by having the experimenter adjust the two visible points on the ruler clips. This adjustment will be done as follows: First, the experimenter will move the top clip downwards at a continuous speed until the participant indicates that the visual point on the clip has reached the fingertip position with a "*Stop*" signal. Following a similar procedure, the experimenter will move the bottom clip upwards at a continuous speed until the participant indicates that the visual point on the clip has reached the knuckle position with a "*Stop*" signal.

Additionally, for each estimation (fingertip and knuckle), the feeling of confidence with the estimations made will be assessed.

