The experimenter will use the measurements on the back of the ruler to record the fingertip and knuckle positions, rounding to the nearest 0.5 cm. After each trial, the clips are relocated. After completing the practice task, the experimental block will begin. Participants will repeat the task for thirty trials. Each experimental tone will be presented ten times. The order of trials will be randomized across participants. Participants will be given the opportunity to rest after each 10 trials.

After the experimental block, participants will be asked to repeat the task for three more trials (one for each sound condition, their order randomized across participants), in order to collect self-report measures (questionnaire block). After each trial, participants will complete a questionnaire that assesses their subjective experience during the task [see Additional file 2].

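### The close-when-full quota is likely to put most subthreshold women after the last control, tying group to session order for the hand-read finger and waist estimates

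*Protocol article*

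**What the plan says.** All places are in the protocol article.

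- **Quota (Participants).** Both groups are open at first; "once the desired participant sample size has been reached for one of the groups, only participants falling into the other group defined" are invited afterwards. Table 1 defines the groups by the S-EDE-Q global score: "we will use a cut-off point ≥ 2.8 as clinically significant".
- **Numbers (Sample size considerations).** The target is "a total of 100 participants (50 participants in each group"). To reach it, "we will screen approximately at least 450 young adult females", a figure attributed to S-EDE-Q norms.
- **Who measures (General experimental procedure).** "The experimental procedures will be implemented, and all data will be collected, by a postgraduate Ph.D. researcher", in the singular.
- **How the ruler outcomes arise.** In Experiment 1, "the experimenter will move the top clip downwards at a continuous speed until the participant indicates" that the position is reached. "The experimenter will use the measurements on the back of the ruler to record the fingertip and knuckle positions", rounded to 0.5 cm. The waist width in Experiment 2 is obtained with the same kind of hand-moved clips and the same rounding.
- **Analysis (Statistical analyses).** The ANOVAs use group and feedback tone, plus time for body size discrepancy. Baseline body size discrepancy is a conditional covariate. Session date or order is not a term.

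What is randomised or counterbalanced is tone order and the starting positions of clips and avatar. All of these act within a session.

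**The concern.** A quota that closes each group as it fills gives equal group sizes but does not balance the groups over time. When one group is much more common in the screening stream, it fills early and the rest of the study tests only the other.

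That matters here because the ruler estimates depend partly on the experimenter. Clip speed combines with the participant's reaction time before the stop signal, and the reading is rounded by eye. Practice and habit can change over 100 sessions of about two hours each. If controls sit mainly in the early sessions and subthreshold women mainly in the late ones, such a change looks like a group difference. In addition, once controls are closed, anyone who knows the quota status knows that each new participant is subthreshold.

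**Working it through.** **Inputs.** 50 per group and about 450 screened (Sample size considerations); the close-when-full rule (Participants); sensitivity 0.95, specificity 0.90 and positive predictive value 0.59, each given as a lower bound (Table 1).

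**Step 1: the plan's own figure.** The article gives no prevalence, so 450 cannot be reproduced. It can be inverted: 50/450 = 11.1% of those screened become subthreshold participants.

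**Step 2: an alternative share from Table 1.** Let π be the prevalence of true cases. Setting 0.95π / [0.95π + 0.10(1 − π)] = 0.59 gives π = 0.132. The screen-positive share is 0.95 × 0.132 + 0.10 × 0.868 = 0.212. These values describe the instrument and are bounds, so this is only a second assumed value.

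**Step 3: sequential filling.** Let p be the share of eligible women scoring at least 2.8, and assume they are tested in the order they screen. Eligible screens needed to fill controls = 50/(1 − p). Subthreshold women enrolled by then = 50p/(1 − p). Share of the subthreshold group still to come = 1 − p/(1 − p).

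The last three rows assume that the 450 already allows for the exclusion criteria, equally in both groups, and still yields 50 subthreshold women.

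| p | Basis | Screens to fill controls | Subthreshold by then | Tested after controls close |
|---|---|---|---|---|
| 0.111 | 50/450, all eligible | 56.2 | 6.2 | 88% |
| 0.212 | Table 1 accuracy values | 63.5 | 13.5 | 73% |
| 0.222 | 50/225, half eligible | 64.3 | 14.3 | 71% |
| 0.278 | 50/180, 40% eligible | 69.2 | 19.2 | 62% |
| 0.370 | 50/135, 30% eligible | 79.4 | 29.4 | 41% |

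The share exceeds one half whenever p/(1 − p) < 0.5, that is p < 1/3. In terms of eligibility this means more than 150 of the 450 eligible, since 50/150 = 1/3.

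**Step 4: simulation at p = 0.111 (3,000 sequences).** On average 43.7 of 50 subthreshold women come after the last control (95% range 38 to 48). The mean gap in session order between groups is 43.6 of 100, and the correlation of group with order is 0.75. With 1:1 pacing, gap and correlation would both be about 0.

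**Step 5: illustration of the consequence.** Drift size is unknown, so assume a linear drift of 0.2 to 0.5 SD over the study. The spurious group difference is drift × 43.6/99:

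- 0.2 SD gives 0.088 SD
- 0.5 SD gives 0.22 SD

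The standard error of a two-group difference with 50 per group is √(2/50) = 0.20 SD. The shifts are therefore 0.44 and 1.10 standard errors, and a nominal 5% two-sided test rejects about 7% and 20% of the time.

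**Step 6: can it be adjusted afterwards?** With a correlation of 0.75, adding session order multiplies the variance of the group effect by about 1/(1 − 0.75²) = 2.3. Adjustment after the fact is expensive.

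**The case against.** **Test order is not stated.** The rule caps group size and is not a testing schedule. Screening comes before the laboratory visit, so mixed invitations from a pool already screened would fit the text and would shrink the confounding. This stands: early testing of controls is likely, not fixed by the plan. But the rule is worded as a rolling closure, and nothing in the article paces the two groups.

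**The size is soft.** The ratio 50/450 is a recruitment yield. If the 450 allows for exclusions on BMI, psychiatric history or medication, the imbalance is smaller. If those exclusions fall mainly on symptomatic women, it grows again. This also stands, and is why a range is given.

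**A reader might infer that every primary comparison is compromised.** The documents do not support that. H2 to H4 concern the illusion and rest on group by tone. Tones are randomised within each session, so additive drift in clip speed or rounding cancels. The tone plays through closed, attenuating headphones, and nothing says the experimenter knows which one is playing. In the Body Visualizer, which serves H1, the participant sets the avatar and the experimenter only records the result; the questionnaires are completed by the participant on a tablet.

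**A reader might also infer that the plan unmasks the experimenter, or that season and grade-point incentives shift with group.** The article does not say who scores the S-EDE-Q, tracks the quota or sends invitations, and masking may be covered in a fuller protocol. It mentions grade points but no seasonal pattern. What can be said is conditional: knowing the quota status reveals group after closure.

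**The exploratory label.** The article uses it to excuse limited power. It does not answer a possible bias, particularly as the results are meant to support the sample size of a later confirmatory study.

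**Conclusion.** The point holds in a limited form. If women are tested roughly as they screen, the quota is likely to place a majority of subthreshold women after the last control: about 88% at p = 0.111 and 73% at p = 0.212. The share falls below half only if about a third or fewer of those screened are eligible (41% at 30%).

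The exposed quantity is chiefly the group main effect on the finger and waist ruler estimates. The group-by-tone interaction is at risk only if drift or expectation changes the size of the illusion itself. The Body Visualizer and questionnaires are less exposed. Whether drift will occur, and how large it would be, cannot be known from the article. The case for changing the rule is that prevention is cheap before recruitment and correction afterwards is poor.

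**What to change.** 1. Replace the close-when-full quota with paced invitations: for each subthreshold woman booked, invite one control in the same short window, until both groups reach 50. Group is known from the S-EDE-Q before the laboratory visit, so this is feasible.
2. Record session date and order, and report a sensitivity analysis of the ruler estimates that includes session order, for instance in a linear mixed model with group and tone. Under pacing, order is nearly uncorrelated with group and the adjustment costs almost no precision.
3. Where existing staff allow, have someone other than the experimenter score the S-EDE-Q and issue coded invitations, so that score and group stay hidden from the experimenter until data lock. Whether someone on the team can take this on is for the investigators to say.

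Matching on age or BMI is not needed for this purpose: it addresses neither session order nor masking, and both variables are already restricted by the entry criteria.

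The cost is scheduling effort, and control recruitment runs over the whole study period instead of finishing early. No additional participants are required.
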